### Problem Statement

ViP recruited its first patient in December 2020 and is in its infancy. While the general program design, processes and guiding principles were drafted by the ViP team with inputs from policy makers, it is not well understood “for whom” the planned program will be suitable and “how” ViP will work and be sustainable in the local context. To the best of our knowledge, ViP is one of the first integrated home PC model for non-cancer patients in Singapore involving an acute hospital, home medical and nursing teams and an inpatient hospice hence there are limited relevant context-specific insights from which ViP can learn from. As such, a rigorous and practical evaluation strategy to address the existing knowledge gaps is warranted. Findings from such evaluation will provide insights to support the implementation and further development of ViP and similar programs in Singapore and beyond.

Commonly used evaluation design, Randomised Controlled trial (RCT) design, which focuses solely on outcomes evaluation is rigid when evaluating a complex intervention. It is unsuitable for evolving interventions and rarely adequately or even explicitly address the context-specific drivers behind any outcomes and their relationship to the underlying program theory [22]. This makes it difficult to interpret their findings for improvement purposes due to its limited relevance in reality. [23].

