3	% of needy patients who were provided support	Administrative database & interviews with caregivers	Quarterly for the first 2 years of the programme					Change in caregiver burden score before and after intervention	Zarit Burden Interview-12	Baseline (at enrolment) and every 3 months after enrolmentuntil patients’ death	

								No. of ED attendances, in-patient admission and length of stay (LOS)	Administrative databases	1 month (30 days), 3 months (90 days) and 6 months (180 days) prior to death	

								% of patients with good management of symptoms	PCOC – symptoms assessment		
	
4	% of cases discussed in the MDM (multidisciplinary meetings)	Administrative database		Providers’ working experience	Interviews with providers	At least 6 months after program implementation		Development costs, program implementation costs and healthcare utilization costs	Administrative database	6 months prior to death	
		
	Quality of collaborative and communications between providers	Interviews with providers						Average duration in each PCOC stage		1 month (30 days), 3 months (90 days) and 6 months (180 days) prior to death	
	
5	Implementation experience	Interviews with providers	At least 6 months after program implementation					Perceived quality of care	Mortality follow-back survey	≤3 months after death	
	
*6*	Extent of support from management							Sustainability	Clinical Sustainability Assessment Tool (CSAT)	At least 6 months after program implementation	

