#### Data Collection

Context, mechanisms and relationships between context and outcomes, as defined in phase 1, will be tested through interviews with healthcare providers and users. As suggested by Manzano [29], questions to be asked in these interviews aim to ascertained how the program works, for whom, in what circumstances and how implementation has veered from what was initially planned. A purposive sample of 15 healthcare providers/managers and 15 healthcare users (patient and/or carers) per disease condition will be invited to take part in face-to-face or virtual interviews. The eventual sample size will be determined based on thematic saturation of the study. Data saturation is reached when the ability to obtain additional new information has been attained, and when further coding is no longer feasible [30].

In ensuring the quality of data collected, an interview guide will be used and interviewers will routinely reflect on interview experience and discuss data as they are being collected. Based on emerging understanding and identification of key knowledge gaps throughout the process of interviewing, interview questions will be revised accordingly.

Healthcare services utilization, health outcomes, healthcare cost and caregiver burden data will be collected and analyzed over time to evaluate intervention outcomes of ViP. A quasi-experimental design will be adopted by comparing the outcomes of the intervention group against a comparator group for healthcare utilization, outcomes and cost. Due to limited data available, a pre-post comparison will be made for caregiver burden. A quasi-experimental design is selected as it more truly mimics real-world constraints and provide a balance between internal and external validity [31]. Pragmatically, all patients who agree to participate, are accepted into the home-based PC service, utilized the services for at least one month and passed away as of December 2022 will be included as the intervention group. A retrospective comparator group will be identified from available CGH and SACH clinical databases. We plan to restrict the databases to within CGH and SACH for the identification of comparators. This is because patients are planned to be recruited from CGH and SACH in the first 2 years. This is a way of ensuring comparability between intervention and comparator group while keeping the data manageable.

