In identifying retrospective comparator group, relevant databases will initially be filtered for individuals who were referred to home hospice services between 2016–2019, have completed their advance care planning (ACP) and have died as of December 2020. Death status will be obtained from National Registry of Diseases Office records. Then, using a propensity matching strategy, a comparator group matched to intervention group in terms of age, gender, ethnicity, functional status, clinical status and re-admission characteristics will be identified. A ratio of 1:1 of intervention to comparator group will be used for matching.

In the assessment of healthcare utilization and health outcomes, date of death will be used as reference point for comparison. Acute hospital utilization (emergency department (ED) attendances, inpatient admissions, intensive care unit (ICU) admissions and length of stay (LOS)) will be extracted backwards from the date of death for 1 month (30 days), 3 months (90 days) and 6 months (180 days). Concordance of actualized place of death with preferences discussed as part of ACP will be determined after death as described by Tan et al [32].

We take a healthcare system perspective in examining the effect of ViP on healthcare cost. Development costs, program implementation costs and healthcare utilization costs will be measured. Development costs include costs incurred during the development of ViP. The program implementation costs consider costs related to the implementation of the program including the manpower, travel, equipment, materials used for patient and caregiver training and costs associated with multidisciplinary team meetings. The development and implementation costs will be systematically collected using the WHO’s CostIt instrument [33] and will be divided by the number of clients enrolled into the program to obtain per patient cost. Healthcare utilization cost for the use of hospital inpatient and outpatient services and primary care services in the metrics of full gross bill amounts will be extracted for six-month period before death.

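### The 90- and 180-day look-backs from death (180-day only for cost) can include substantial time before ViP enrolment, and the plan analyses it as programme outcome

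*Protocol article*

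**What the plan says.** All references are to the Protocol article.

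- **Who is counted.** Under Data Collection, the intervention group is made up of consenting, accepted patients who "utilized the services for at least one month and passed away as of December 2022 will be included as the intervention group".
- **Time anchor.** For utilisation and health outcomes, "date of death will be used as reference point for comparison". This applies to both groups.
- **Utilisation windows.** ED attendances, admissions, ICU admissions and length of stay "will be extracted backwards from the date of death for 1 month (30 days), 3 months (90 days) and 6 months (180 days"). Table 2 repeats the windows as "1 month (30 days), 3 months (90 days) and 6 months (180 days) prior to death" and also gives them to the average duration in each PCOC stage.
- **Cost window.** Utilisation cost "will be extracted for six-month period before death". There is no 90-day cost window.
- **Matching.** Comparators are matched on "age, gender, ethnicity, functional status, clinical status and re-admission characteristics". The time at which these are measured is not stated.
- **Analysis.** Data Analysis uses Poisson or negative binomial regression for counts to estimate the programme's effect, and mentions a sensitivity analysis without describing it.

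Nothing in the article restricts counting to time after enrolment, gives comparators an index date, requires service as long as the window, or adjusts for days enrolled.

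**The concern.** ViP cannot change an admission, ED visit or bill that occurred before the patient enrolled. When the minimum exposure is one month and the window is three or six months, such events enter the outcome. The section on the intervention says that patients are identified partly while in hospital, so the referring admission itself can be counted as a ViP outcome.

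Reducing unnecessary acute utilisation and keeping cost affordable are stated aims of ViP, and effectiveness is one of the research questions. The 180-day utilisation and six-month cost results are the most exposed. For cost, the full per-client development and implementation cost would be set against bills that partly predate the programme.

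The PCOC measures have a related problem. PCOC assessment is described only after enrolment, and pre-assessment by a palliative care team is not required for referral. The article therefore describes no source of PCOC data for the earlier part of a 90- or 180-day window.

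**Working it through.** The article gives no effect size, event rate or enrolment-to-death time for this comparison, so there is no stated figure to reproduce.

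**Inputs from the article**
- Minimum ViP use: one month, taken as 30 days.
- Windows *W*: 30, 90 and 180 days before death; cost about 180 days.
- Longest possible tenure: "ViP recruited its first patient in December 2020" and death is required by December 2022, so about 24 months.

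**Step 1: share of one patient's window before enrolment (no distributional assumption).** With enrolment *T* days before death, the share is s = max(0, W − T)/W.

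| *T* (days) | *W* = 30 | *W* = 90 | *W* = 180 |
|---|---|---|---|
| 30 | 0 | 60/90 = 67% | 150/180 = 83% |
| 60 | 0 | 30/90 = 33% | 120/180 = 67% |
| 90 | 0 | 0 | 90/180 = 50% |
| 120 | 0 | 0 | 60/180 = 33% |
| ≥180 | 0 | 0 | 0 |

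**Step 2: average share (assumed tenure).** Assume exponential enrolment-to-death time with median 2, 3 or 6 months and enrolment uniform over 24 months. Keep those with at least one month of service and death by month 24. Coverage is c = E[min(T, W)]/W, and the pre-enrolment share is 1 − c.

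| Median | c, 90 d | before enrolment | c, 180 d | before enrolment |
|---|---|---|---|---|
| 2 months | 0.793 | 21% | 0.527 | 47% |
| 3 months | 0.841 | 16% | 0.607 | 39% |
| 6 months | 0.893 | 11% | 0.712 | 29% |

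In these scenarios 61–87% of ViP decedents have less than 180 days of service.

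**Step 3: effect on the estimate (assumed true rate ratio 0.70, even event rate, pre-enrolment ratio 1.0).** Observed RR = 0.70c + 1.0(1 − c).
- 90 days: 0.70 × 0.793 + 0.207 = 0.76; 0.70 × 0.841 + 0.159 = 0.75; 0.70 × 0.893 + 0.107 = 0.73.
- 180 days: 0.70 × 0.527 + 0.473 = 0.84; 0.70 × 0.607 + 0.393 = 0.82; 0.70 × 0.712 + 0.288 = 0.79.

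**Step 4: sensitivity to the assumptions**
- *Tenure shape.* With T = 30 days plus an exponential excess and mean tenure from 270 down to 60 days, the average pre-enrolment share is 8–38% (90 days) and 21–67% (180 days). The assumed 0.70 then reads 0.72–0.81 and 0.76–0.90.
- *Use concentrated near death.* With event rates of 3:2:1 for days 0–30, 31–90 and 91–180, the Step 3 range at 180 days becomes 0.76–0.80.
- *Pre-enrolment imbalance.* For T = 30 and W = 180, observed RR = (5/6) × RR_pre + (1/6) × 0.70. RR_pre of 0.8, 1.0 and 1.3 gives 0.78, 0.95 and 1.20.

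**The case against.** Anchoring on death is an explicit choice, applied to both groups, and no window is named as primary. The 30-day window has no pre-enrolment time for a patient with at least 30 days of service. It is largely free of the problem provided service continued to death, which the inclusion rule does not strictly require because patients may withdraw. The introduction notes that non-cancer patients often outlive their prognosis, so tenure could be long. All of this stands, and it limits the size of the problem. It does not remove it, because the one-month rule and the windows are fixed in the text and an analysis that followed them would carry it.

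A reader might infer more than the article supports:

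- *That most of the measured outcome precedes enrolment.* Tenure is not reported. Two thirds and five sixths are the extremes for a patient at the one-month minimum, and under the Step 2 assumptions only 11–21% of the 90-day window is affected.
- *That the effect is necessarily pulled toward no difference.* That needs balanced pre-enrolment use, which is not shown.
- *That cost is also counted over 90 days.* It is not.
- *That the matching conditions on the outcome.* This would follow only if re-admission characteristics were measured inside the look-back. The article does not say, and such detail is commonly left to a fuller document.
- *That the study cannot show whether ViP works.* The shorter windows are little or mildly affected under the Step 2 assumptions.

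**Conclusion.** The point holds as a structural fault in the 90- and 180-day utilisation windows and the six-month cost window. As written, up to 67% of a patient's 90-day window and 83% of the 180-day window can precede ViP and still count as programme outcome. This part rests only on the article's own figures and is firm.

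The average size is conditional. With medians of 2–6 months, even event rates and balanced pre-enrolment use, an assumed true ratio of 0.70 reads about 0.73–0.76 at 90 days and 0.79–0.84 at 180 days. The distortion is mild at 90 days and material at 180. If pre-enrolment use differs between the groups, the direction is not fixed, and in the extreme case shown even the sign can change.

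**What to change.** 1. Define the same index event in both groups: for example, referral to the home service in both, or first home visit in both if the comparator data hold it. Enrolment for ViP against referral for comparators would not be like for like, because ViP enrolment comes after referral, vetting, an assessment visit and a signed agreement.
2. In each window, count utilisation and bills from the later of the index date and the window start up to death, with log(days at risk) as an offset in the planned count models.
3. An offset alone assumes an even rate, and rates may rise near death. Therefore also balance or adjust for index-to-death time, or restrict each window to matched patients whose index date is at least that long before death.
4. Measure re-admission characteristics and pre-index utilisation before the index date, and use them in the propensity score.
5. Report PCOC measures for time after enrolment only.
6. Keep the full death-anchored windows as descriptive secondary results, and report the distribution of enrolment-to-death time.

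**Cost.** No new patient contact is needed. ViP enrolment is a recorded event, and comparators are already selected by referral. Whether a first-visit date exists for comparators must be checked before that option is chosen. If referral is the index, the ViP days between referral and enrolment stay in the count; that is the price of comparability. There will be fewer counted events and somewhat wider intervals at 180 days.

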Data for both intervention and comparator group will be extracted from SingHealth-iHiS Electronic Health Intelligence System (eHints), a common database of patient level data across all SingHealth institutions. Development and implementation cost will be extracted from ViP program database and potentially finance department. For comprehensiveness, we may also merge dataset with data held by the Ministry of Health to obtain nationwide acute hospital utilization (ED visits, hospital admissions, ICU utilizations, length of stay and date of death) using National Registration Identification Card (NRIC) of subjects included in the study.

Primary informal caregivers of ViP patients will be invited to complete a Zarit Burden Interview (ZBI) – 12 items to assess caregiver burden at enrolment and every 3 months after enrolment until patients’ death. The ZBI is a widely used tool for assessing caregiver burden among those who provide care for patients with various illnesses, including those at the end-of-life [34,35]. A higher score on the ZBI represents higher burden. As suggested by Stagg and Larner, a score of “0–20”, “21–40” and “>40” will be considered as little or no, mild/moderate and high caregiver burden respectively [36].

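### The planned cost comparison counts ViP's home palliative care but not the comparator's home hospice care, and its programme costs and bills rest on different denominators and windows, so it risks bias

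*Protocol article*

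**What the plan says.** All of this is in the protocol article, Methodology, Phase 2, Data Collection, unless noted.

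- **Comparison and perspective.** The quasi-experimental design means "comparing the outcomes of the intervention group against a comparator group for healthcare utilization, outcomes and cost". On cost: "We take a healthcare system perspective in examining the effect of ViP on healthcare cost".
- **Cost types.** "Development costs, program implementation costs and healthcare utilization costs will be measured".
- **ViP programme cost.** Implementation covers "costs related to the implementation of the program including the manpower, travel, equipment, materials used for patient and caregiver training", as well as team meetings. Development and implementation costs together "will be divided by the number of clients enrolled into the program to obtain per patient cost". Their source: "Development and implementation cost will be extracted from ViP program database and potentially finance department".
- **Utilisation cost.** "Healthcare utilization cost for the use of hospital inpatient and outpatient services and primary care services in the metrics of full gross bill amounts", taken over the six months before death.
- **Comparator.** "relevant databases will initially be filtered for individuals who were referred to home hospice services between 2016–2019"; they must also have completed advance care planning and have died by December 2020.
- **Analysed ViP group.** Patients who agreed to take part, used the service for at least one month and died by December 2022.
- **Table 2.** The cost row, under program theory 4, puts development, implementation and utilisation costs into one outcome indicator, measured six months prior to death.

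**The concern.** A healthcare system perspective requires the same kinds of care to be costed in both groups. ViP's manpower, travel, equipment and meetings are the cost of delivering palliative care at home. The comparator's counterpart is home hospice care; the Background says that home palliative care in Singapore has come mainly from specialist home hospice providers. That care appears neither among the cost items nor in the data sources. One group's home care is priced and the other's is not.

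The second problem is that the two cost components describe different people and different periods. Programme cost is spread over everyone enrolled. Bills belong to a narrower set of decedents and a fixed window.

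Keeping cost affordable is one of ViP's stated aims, program theory 4 predicts reduced healthcare cost, and the Discussion addresses the findings to policy makers. A cost difference built on unlike quantities could mislead on each of these.

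**Working it through.** The article states no cost, cost difference, unit cost or number of enrolees, so there is no figure to reproduce. The check is structural. Every number below is an illustration on assumed inputs.

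**1. Is home hospice captured anywhere?**

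| Item | ViP | Comparator |
|---|---|---|
| Home palliative care delivery | Counted, from the ViP database and possibly finance | Not listed, no source named |
| Hospital inpatient and outpatient, primary care bills | Counted | Counted |

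The optional merge with Ministry of Health data covers acute hospital use and date of death only, so it does not fill the empty cell.

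**2. Size of the asymmetry if totals are compared.** Let U_V and U_C be mean bills per patient, P the ViP programme cost per patient, and H the mean home hospice cost per comparator (non-recipients count as zero).

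- Difference on the listed items: (U_V + P) − U_C
- Difference with home care in both groups: (U_V + P) − (U_C + H)
- Overstatement of ViP's excess: the first minus the second = H

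With equal bills, U_V = U_C = 100:

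| P | Difference on listed items | Symmetric, H = 0 | Symmetric, H = 0.5P | Symmetric, H = P |
|---|---|---|---|---|
| 10 | +10 | +10 | +5 | 0 |
| 20 | +20 | +20 | +10 | 0 |
| 30 | +30 | +30 | +15 | 0 |

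**3. Denominator.** Let T be total programme cost, N the number enrolled and n the number analysed, with f = n/N. The planned figure is P = T/N.

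- If the analysed patients bore all of the cost, the figure per analysed patient is T/n = P/f. For f = 0.4, 0.6, 0.8 and 1 the multiplier is 2.5, 1.67, 1.25 and 1.0.
- If cost is apportioned by service time, the multiplier is k, the mean service time of analysed patients divided by that of all enrolees. Illustrative values of 0.75 to 1.5 lie on both sides of 1.

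**4. Window.** The text sets the six-month window for bills but states none for programme cost, so that cost in effect covers the whole stay. Restricting it to the window multiplies it by w, the share of analysed patients' service time that falls inside. If every patient were served for the 12 months before death, w = 6/12 = 0.5; if all service fell within the last six months, w = 1. The combined factor k × w then runs from 0.75 × 0.5 = 0.375 to 1.5 × 1 = 1.5. The planned per-patient figure could be too high or too low.

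**5. Table 2 against the text.** Table 2 applies the six-month window to all three cost types; the text applies it to utilisation alone. Development cost is spent on building the programme, not in a given patient's last six months, so the Table 2 entry cannot be applied to it literally.

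**The case against.** The strongest reply is that the article defines no incremental cost. It says that three cost types are measured and names separate sources. Comparing bills between groups and reporting programme cost alongside fits the text equally well. This stands: a reader might infer that the plan's incremental cost is wrong, but no formula exists to be wrong. It does not remove the point. Table 2 treats the three types as one outcome, and cost is declared a between-group comparison. If only bills are compared, home care is missing from both groups, which does not meet the stated perspective.

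A reader might also infer that every comparator received home hospice, so that the bias is large. The text says referred, not served, so H is unknown and could be small. Nor does the text support an overall bias against ViP of fixed sign, because the denominator and window effects can go either way.

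A further tempting reading is that unadjusted bills are compared across years. The periods do differ: comparators died by December 2020, whereas ViP took its first patient in December 2020 and counts deaths to December 2022. But the article is silent on price year, a detail that an article commonly leaves to the full protocol or analysis plan. Any percentage drift would need a growth rate and a spread of death dates that are not given. This is a point to confirm, not a stated error.

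Finally, it may be said that the cost items too are condensed. The article nevertheless fixes the perspective, the comparator, the cost items and the sources, and these do not fit together.

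**Conclusion.** The concern holds as a risk of bias in the cost comparison. Home palliative care is costed for ViP but lies outside the listed items and sources for the comparator. If totals are compared, ViP's excess is overstated one-for-one by the mean home hospice cost per comparator. That amount cannot be sized from the article and is zero only if none received the service. The mismatch of denominator and window is also visible in the text, as is the disagreement between Table 2 and Data Collection; its direction is not fixed. The plan should be changed on both counts before cost results are interpreted.

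**What to change.** 1. **Make the comparison symmetric.** Either add home hospice cost for comparators, at actual charges or at a unit cost per patient-month shown with a range; or limit the between-group comparison to utilisation bills, report programme cost separately, and state that home care is excluded for both groups.
2. **Align people and time.** Express ViP implementation cost per patient-month of service and apply it to the analysed patients' service months inside the six-month window. Report development cost separately as a one-off.
3. **Reconcile Table 2 with Data Collection** on which cost types carry the six-month window.
4. **Confirm** that bills are put on a common price year.

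The cost is modest analytic work: a home hospice unit cost and a service-month denominator from the programme database, with no new recruitment. The downside is that the home hospice unit cost may have to be an estimate, which is why a range is needed.

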### The Intervention: Violet Program

The Violet Program (ViP) was developed as a collaboration between Changi General Hospital (CGH) and St. Andrew’s Community Hospital (SACH) to provide home-based PC to non-cancer patients residing in the Eastern region of Singapore. VIP aims to (i) reduce unnecessary acute hospital utilization (ii) improve health outcomes (iii) reduce caregiver burden through caregiver support (iv) honour patient preferences better through integrated care while (v) keeping healthcare cost affordable.

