**Figure 1 F1:**
[figure not shown]
Recruitment workflow of ViP.

After enrolment, care is then stratified according to needs based on Palliative Care Outcomes Collaboration (PCOC) assessment [21]. Patients of higher acuity or requiring closer monitoring will be cared for by the specialists. Patients deemed more stable will be serviced by the generalists with ad-hoc visits by the specialists to manage acute deteriorations. For every patient enrolled, an individualized care plan is developed, revisited regularly and executed collaboratively by healthcare providers and patients/carers. Patients are contacted at least once a month via phone call, video call or home visit. Frequency of contact is guided by PCOC assessment at each contact. Weekly multidisciplinary team meetings are held to discuss new, complex cases and to review mortalities as a formal debrief and to identify bereavement needs. Allied health, community-based service providers or lay extenders are engaged to provide an additional layer of support for patient or caregiver depending on patient/carers’ needs. Service is provided from enrolment until (i) the patient passes away and bereavement support is no longer required, (ii) patient’s condition improves and/or stabilizes such that the patient is no longer deemed to suffer from a terminal illness and home PC support is not required, (iii) patient is admitted to an inpatient hospice for terminal care or admitted to the acute hospital for more than three months, (iv) patient or family requests to withdraw from the service and (v) patient moves out of the zone of coverage.

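### Acute hospital use comes from one cluster's database, nationwide linkage is optional and comparators have no residence criterion, so capture of events can differ between groups

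*Protocol article*

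**What the plan says.** **Data source.** Under Data Collection, the data for both groups are to be extracted from eHints, described as "a common database of patient level data across all SingHealth institutions". The next step is conditional: "we may also merge dataset with data held by the Ministry of Health to obtain nationwide acute hospital utilization". The article lists the items this linkage would supply (ED visits, admissions, ICU use, length of stay, date of death) and the identifier to be used. It does not say when the linkage would or would not be done.

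**Intervention group.** The section on the intervention says ViP was set up "to provide home-based PC to non-cancer patients residing in the Eastern region of Singapore". One of the listed reasons for ending the service is that the "patient moves out of the zone of coverage".

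**Comparator group.** Data Collection states: "We plan to restrict the databases to within CGH and SACH for the identification of comparators". The reason given is that ViP patients are planned to come from those two institutions, and the article presents this as its means of securing comparability. The first selection step keeps only these people: "individuals who were referred to home hospice services between 2016–2019, have completed their advance care planning (ACP) and have died as of December 2020". Comparators are then "matched to intervention group in terms of age, gender, ethnicity, functional status, clinical status and re-admission characteristics", at a 1:1 ratio. Residence is in neither list.

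**Use of the data.** ED attendances, admissions, ICU admissions and length of stay are counted back 30, 90 and 180 days from death, and bills over six months. Data Analysis assigns Poisson or negative binomial regression to counts.

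**The concern.** An acute event at a hospital outside the cluster does not appear in eHints and enters the analysis as no event. If that happened equally often in both groups, the rate ratio would be unaffected. The plan does not secure this equality: living in the East is tied to receiving ViP, while a comparator only has to appear in a CGH or SACH database. Where a patient was identified does not settle where that patient lived, or where they sought acute care in the last 180 days of life.

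Reducing unnecessary acute hospital use is the first aim listed for ViP. Utilisation and its cost are main outcomes of the only part of the evaluation with a comparator group; caregiver burden is compared before and after only. No listed matching variable describes place of residence, and the regression cannot restore events that were never recorded. The cost analysis is also described as taking a healthcare system perspective, which one cluster's bills do not fully provide.

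**Working it through.** The plan gives no capture rate, effect size or sample size for this comparison, so there is no figure to reproduce. The check has three steps.

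**1. Is there an asymmetry in the text?**

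| Feature | ViP group | Comparator group |
|---|---|---|
| Institution | Planned recruitment from CGH and SACH; other organisations 7.5% of referrals as of May 2022 | CGH and SACH databases |
| Residence | Eastern region | No criterion |
| Outcome source | eHints (SingHealth) | eHints (SingHealth) |
| Nationwide linkage | Optional | Optional |

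Institution and outcome source are aligned. Residence is not.

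**2. What would unequal capture do to the rate ratio?** Let *c* be the share of a group's acute events that eHints records. The expected recorded count is *c* times the true count, so

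observed ratio = true ratio × *c*(ViP) / *c*(comparator).

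All capture values below, and the true ratio of 0.85, are assumptions.

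| *c*(ViP) | *c*(comparator) | Factor | Observed ratio if the true ratio is 0.85 |
|---|---|---|---|
| 95% | 95% | 0.95/0.95 = 1.00 | 0.85 |
| 95% | 90% | 0.95/0.90 = 1.06 | 0.90 |
| 95% | 85% | 0.95/0.85 = 1.12 | 0.95 |
| 95% | 80% | 0.95/0.80 = 1.19 | 1.01 |
| 85% | 95% | 0.85/0.95 = 0.89 | 0.76 |

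The first row shows that equal capture gives no bias; incomplete but equal capture, such as 90% in both groups, also gives a factor of 1.00. The last row shows the opposite error, in which ViP looks better than it is.

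**3. What would it take to produce such a gap?** Suppose Eastern residents are captured at 95% in both groups. Let *p* be the share of comparator events that belong to residents elsewhere, and *d* the drop in capture for those events. The gap is then *p* × *d*. A 5-point gap needs *p* × *d* = 0.05, and a 15-point gap needs 0.15. Since *d* cannot exceed 0.95, *p* must be at least 0.05/0.95 = 5% and 0.15/0.95 = 16% respectively. It must be larger to the extent that these patients, who were known to CGH or SACH, still use SingHealth hospitals. The article gives neither *p* nor *d*.

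**The case against.** The strongest reply is that the comparator group is not an open one. It comes from the two institutions that supply most ViP referrals (100 − 7.5 = 92.5% as of May 2022), and the article adopts this restriction for comparability. Both groups are read from the same database. That database spans the whole cluster, so care at another SingHealth hospital is still counted. This stands, and it makes a large gap less likely. It does not make capture equal, because it fixes where patients were identified and not where they lived.

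The rule ending service on leaving the zone is weaker support than it first appears. The analysed ViP group needs only one month of service and death by December 2022, so someone who later moved away could still be included.

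Matching on re-admission characteristics can work either way. If these come from eHints, they share any under-recording. They may also select comparators with similar recorded in-cluster use, which would reduce a gap.

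Conditional wording is understandable when another body holds the data, and the filter is described as an initial one in a condensed article. Even so, the article states the source, the filter and the matching variables outright, and residence is absent from what it states.

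A reader might infer that the documents show comparators to be under-recorded, so that a ViP benefit would be hidden or reversed. They do not. No passage says how many comparators live outside the East or where they seek acute care, and the reading above 1 needs the widest gap in the table.

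**Conclusion.** The point holds as a possibility that the plan leaves open, not as a demonstrated bias. The outcome source covers one cluster, the nationwide source is optional, and the programme's own residence condition is not carried over to the comparators. Capture of ED visits, admissions, ICU use, length of stay and bills can therefore differ between groups.

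Size and direction are unknown. From a starting capture of 95%, a 10-point shortfall in comparators multiplies the ratio by 1.12, and the same shortfall in ViP multiplies it by 0.89. These factors rest on assumed capture rates and on missed events being counted as none. The CGH and SACH restriction probably keeps the gap smaller than an unrestricted pool would. The change is worth making because it removes an avoidable asymmetry, using a criterion and a data source that the article already names.

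**What to change.** 1. Add residence in the ViP catchment at the time of referral to the comparator filter. If the pool becomes too small for 1:1 matching, use residence as a matching variable instead.
2. Make the nationwide linkage, whose items are already listed, the primary source of acute utilisation in both groups. Report the share of acute use outside the cluster by group; this replaces the assumed capture rates above with observed ones.
3. If linkage is not granted, label the utilisation and cost outcomes as use within SingHealth. The listed linkage items do not include bills, so the cost outcome needs that label even with linkage unless bills from outside the cluster are also obtained. The residence criterion is then the main protection for the cost comparison.

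**Cost.** The comparator pool shrinks by an amount that cannot be judged from the article. It may matter, because the Introduction says non-cancer patients were referred to home palliative care much less often and comparators must also have completed advance care planning. The linkage takes approval time.
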